**Figure 3. F3:**
[figure not shown]
Schematic diagram of quantify traction and set traction angle.

### 2.5.
*Observation indicators and outcomes*

#### 2.5.1.
*Physical data*.

In the process of traction therapy, the following data needs to be recorded: use the load cell to record the traction load; use an infrared range finder to measure the moving distance of the body under traction; record the stretching distance of the lumbar spine on the skin surface through a strain sensor; record dynamic heart rate and surface electrical signal through electrocardiograph and 8-channel electromyography; use angle measuring instrument to record traction angle. All output data will be sorted and managed by a dedicated person.

#### 2.5.2.
*Clinical outcomes*.

The outcome of treatment will be observed at the 4th week and 8th week after the whole course of treatment. Adverse events will be monitored throughout the study period. In addition, the following tests will be performed respectively at weeks 1, 6, 10, and 14: complete blood count; liver and renal function tests; blood coagulation test; urinalysis; and pregnancy test (if necessary).

The primary outcome will be a change in the intensity of low back pain. We plan to use the 100-mm visual analogue scale (VAS) to evaluate the intensity of low back pain: 0 means absence of pain, 100 means worst pain imaginable.^[23]^ We will ask participants to record their pain intensity within the past week by the 100-mm VAS at the following time points: pretrial screening, weeks 1 (baseline), week 6 (primary endpoint), and at weeks 10 and 14 (follow-up sessions). Change from baseline after 6 sessions of treatment will be compared between the groups as the primary outcome.

The secondary outcomes will be the Roland-Morris disability questionnaire (RMDQ), Oswestry disability index, 36-Item short form (SF-36) Health Survey, and adverse events.^[24–26]^ The RMDQ contains 24 sentences that people have used to describe themselves when they have low back pain, and participants check the sentences to describe their life on the day. The ODI questionnaire consists of 10 sections: pain; personal care; lifting; walking; sitting; standing; sleeping; sex life; social life; and traveling. We plan to use the RMDQ to assess the dysfunction in daily life and use the ODI to assess the inability to function in daily life due to low back pain at weeks 1, 6, 10, and 14. The SF-36 is a very popular instrument for evaluating Health-Related Quality of Life. The SF-36 measures 8 scales: physical functioning, role physical, bodily pain, general health, vitality, social functioning, role emotional, and mental health. We will ask participants to record their quality of life by the 100-mm VAS at the following time points: weeks 1, 6, 10, and 14.

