### 2.1. Trial design

This trial is designed as a pragmatic double-center, single-blind, and 3-arm (1:1:1 ratio) RCT to evaluate the effects of self-gravitation traction on LDH patients. The trial is being conducted in 2 hospitals in Lanzhou, China (Affiliated Hospital of Gansu University of Chinese Medicine and Gansu Provincial Hospital of Traditional Chinese Medicine). The recruited LDH patients are randomly allocated into the intervention group (traction load is 40% or 60% of their body weight) or control group (Traction weight is 20% of its body weight).^[18,20,22]^ Traction treatment procedure is completed within 6 consecutive weeks (3 times a week), 10 minutes’ traction for the first 3 weeks, then increase to 20 minutes for the next 3 weeks. See details in Figure 1.

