### 2.3.
*Randomization and blinding*

The study adopts a central stratification and block randomization design. Patient is randomized to the study once they meet the eligibility criteria in which randomization sequence will be generated through SPSS software, version 21 (SPSS Inc. Chicago, IL). The study site of each hospital receives its randomization lists once a week from the primary study center. The randomization sequence cannot be edited and is concealed from the researcher. The aforesaid process of randomization ensures the objectivity of the researcher and eliminates bias in allocating participants groups. After the completion of blind editing, a document is prepared to record the entire process of blind editing, and the 2 copies of the blind secret will be stored in the primary study center and the application hospitals. When the study is completed, the staff who saves the blind bottom from the primary study center will do the first unblinding to get the group code, such as the experimental group or the control group. Afterward, statical data analysis will be done accordingly. Once analysis is completed, the researcher of the application hospital conducts a second unblinding and learns the 3 groups under specific interventions.

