### 2.6.
*Statistical analysis*

After the experiment is completed, we will establish an experiment-related database. The software of SPSS, version 21 (SPSS Inc. Chicago, IL) will be used for statistical analysis, and measurement data will be expressed by Mean and Standard Deviation (mean ± SD). The independent t-test and Chi-square test will be used to compare differences in general characteristics between the groups. All statistical analyses will be performed using PASW statistics 18 for Windows, and the statistical significance level will be considered to be 0.05 (2-sided), with 95% confidence intervals.

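### The primary comparison is stated as change from baseline in VAS between groups, with no adjustment for baseline VAS or the randomisation strata stated; a baseline-adjusted ANCOVA would generally be more precise and needs no new data

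*Protocol article*

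**What the plan says.** Section 2.5.2 (Clinical outcomes) sets the primary comparison: "Change from baseline after 6 sessions of treatment will be compared between the groups". VAS is recorded at screening, at week 1 as baseline, at week 6 as the primary endpoint, and at weeks 10 and 14. (The quoted sentence counts sessions where the schedule counts weeks. I take week 6 as the primary time point; the argument is the same at either time.)

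Section 2.3 says: "The study adopts a central stratification and block randomization design". It does not name the stratification factors. Section 2.1 gives two hospitals, so centre is a plausible factor, but the article does not say that it is one.

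Section 2.6 gives software, summary statistics, a two-sided 0.05 level and two tests. Their use is limited: "The independent t-test and Chi-square test will be used to compare differences in general characteristics between the groups". No section names a test or model for the primary outcome. None mentions a covariate, a stratum or a centre term, and none rules them out.

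**The concern.** A change score uses baseline VAS by subtracting all of it, which fixes the baseline coefficient at 1. ANCOVA estimates that coefficient from the data. When the true slope of week-6 VAS on baseline VAS is not 1, subtraction leaves baseline-related noise in the estimate. It also lets a chance difference in baseline pain between arms carry through to the result. With a slope below 1, the arm that starts higher will tend to show the larger fall whatever its traction load.

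Chance differences in baseline pain are possible. The eligibility criteria in section 2.2.1 set no VAS threshold, section 2.2.3 recruits both outpatients and inpatients, and baseline VAS is not named as a stratification factor.

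The stake is efficiency: wider confidence intervals and lower power for contrasts among the three traction loads than the same 300 patients could give.

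**Working it through.** **Inputs from the article.** 100 patients per arm, 1:1:1 (section 2.2.2); two-sided 0.05 (section 2.6); baseline and week-6 VAS both recorded (section 2.5.2).

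**Inputs not in the article, so assumed.** The correlation r between baseline and week-6 VAS, taken as 0.3, 0.5 and 0.7; the two SDs, s0 at baseline and s1 at week 6, taken as equal at first; and 80% power on change scores, as a reference point only.

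**The plan's own figure.** The sample size of 300 cannot be reproduced, because section 2.2.2 gives no effect size, SD, power or dropout. Back-solving 100 per arm at two-sided 0.05 gives a detectable standardised difference of 0.396 at 80% power or 0.458 at 90%. That restates the sample size and does not check it.

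**Step 1, general result.** Per-patient variance:

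- change score: s0² + s1² − 2·r·s0·s1
- ANCOVA, large samples: s1²·(1 − r²)
- difference: s0² − 2·r·s0·s1 + r²·s1² = (s0 − r·s1)²

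The difference is never negative. In large samples the unadjusted change score is therefore never more precise than ANCOVA, and it is equally precise only when s0 = r·s1.

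**Step 2, equal SDs.** With s0 = s1 = s, the variances are 2(1 − r)s² and (1 − r²)s², so the ratio is (1 + r)/2. The equivalent number per arm is 100/ratio. Power for a pairwise contrast that has 80% on change scores is Φ((1.960 + 0.842)/√ratio − 1.960).

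| r | 2(1 − r) | 1 − r² | Variance ratio | SE ratio | Equivalent n per arm | Power |
|---|---|---|---|---|---|---|
| 0.3 | 1.40 | 0.91 | 0.65 | 0.81 | 154 | 93.5% |
| 0.5 | 1.00 | 0.75 | 0.75 | 0.87 | 133 | 89.9% |
| 0.7 | 0.60 | 0.51 | 0.85 | 0.92 | 118 | 86.0% |

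Put the other way, the change-score variance exceeds the ANCOVA variance by about 54%, 33% and 18% (1/0.65, 1/0.75, 1/0.85). A simulation with 100 per arm and 4000 runs for each r gave variance ratios of 0.653, 0.744 and 0.857.

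**Step 3, unequal SDs.** With k = s0/s1 the ratio is (1 − r²)/(1 + k² − 2rk). At r = 0.5:

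- k = 1: 0.75/1.00 = 0.75
- k = 0.7: 0.75/(1 + 0.49 − 0.70) = 0.75/0.79 = 0.95
- k = 0.5: 0.75/(1 + 0.25 − 0.50) = 0.75/0.75 = 1, no gain
- k = 1.2: 0.75/(1 + 1.44 − 1.20) = 0.75/1.24 = 0.60

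So the gain shrinks as the baseline SD falls below the week-6 SD, vanishes at k = r, and grows if the baseline SD is the larger one.

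**Step 4, chance imbalance.** With equal SDs, an observed baseline difference d between two arms shifts the expected difference in change by (1 − r)·d in magnitude. At r = 0.5 and d = 0.2 SD this is 0.5 × 0.2 = 0.1 SD. ANCOVA removes this shift when the linear model holds.

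**Step 5, strata.** The gain from including the strata depends on how prognostic they are. The factors are not named, so no figure can be given.

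**The case against.** The strongest reply is that section 2.5.2 defines an endpoint and leaves the model open. An ANCOVA with change as the response also compares change from baseline between groups, so the sentence could stand unaltered under the proposed analysis. A condensed article commonly leaves the covariate list to a fuller protocol or analysis plan, which is not shown here. It may already specify adjustment.

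Much of this stands. Adjustment is unstated, not excluded. A change score does use baseline VAS, by subtraction; what is unstated is its use as a covariate. The unadjusted comparison is also valid: under randomisation it is unbiased, and chance imbalance affects it only conditionally. The magnitudes rest on an assumed r and on equal SDs, and Step 3 shows that the gain can be small.

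A reader might go further and infer from section 2.6 that the primary outcome will be analysed by a t-test that ignores stratification by centre, so that its standard error does not match the randomisation. The documents do not support that. The t-test is assigned to general characteristics only, and centre as a stratum is an inference from there being two hospitals.

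The reply does not remove the core point. The article states the form of the primary comparison, and the text followed as written leads to an unadjusted comparison of change. A better analysis is available from data already collected. If a fuller plan does specify adjustment, the published statement should agree with it.

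**Conclusion.** The point holds as a recommendation about efficiency. The primary comparison is stated as change from baseline between groups, no model is named, and no adjustment for baseline VAS or for the strata is stated. Carried out that way it would be unbiased but generally less precise than ANCOVA.

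The direction does not depend on the assumed values: in large samples the change score cannot be the more precise of the two. The size does. The range of 0.65 to 0.85 for the variance ratio is an illustration under equal SDs and r between 0.3 and 0.7, and is not a property of this trial. The power figures rest, in addition, on the assumed 80% reference. No size can be put on the contribution of the strata.

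**What to change.** State in section 2.6, and align section 2.5.2 with it, that the primary analysis is an ANCOVA of week-6 VAS (or of change to week 6; the arm contrasts are the same once baseline is in the model) on arm with three levels, baseline VAS, and the stratification factors actually used in the randomisation. Name those factors in section 2.3 and include centre if it is one of them. Use the analogous model, each with its own baseline, for RMDQ, ODI and the SF-36 scales.

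The cost is wording only. The baseline of each of these measures is already scheduled at week 1, the model runs in standard software such as that already named, and no patient, visit or measurement is added. The choice should be fixed before outcome data are compared by arm. If an existing analysis plan already specifies this model, quoting it in the article is enough.

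### The protocol names the eight-scale SF-36 as a secondary outcome but says quality of life is recorded on a 100-mm VAS, which cannot yield those scales; the two statements must be reconciled

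*Protocol article*

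**What the plan says.** All the relevant text is in section 2.5.2 (Clinical outcomes) of the protocol article.

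- The list of secondary outcomes includes the "36-Item short form (SF-36) Health Survey, and adverse events", alongside the RMDQ and the ODI.
- The instrument is then described: "The SF-36 measures 8 scales: physical functioning, role physical, bodily pain, general health, vitality, social functioning, role emotional, and mental health".
- The next sentence gives the recording method and the schedule: "We will ask participants to record their quality of life by the 100-mm VAS" "at the following time points: weeks 1, 6, 10, and 14".
- The only 100-mm VAS that the article defines is the primary outcome's pain scale, on which "0 means absence of pain, 100 means worst pain imaginable".
- The sentence that sets up that pain measurement has almost the same form: "We will ask participants to record their pain intensity within the past week by the 100-mm VAS".

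For the RMDQ and the ODI, the same section says that the questionnaires themselves are used at weeks 1, 6, 10 and 14. No matching sentence says that participants fill in the SF-36.

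**The concern.** The instrument and the way of recording it do not fit together. The SF-36 is a multi-item questionnaire whose answers are scored into several scales. A VAS is one mark on a line. The VAS sentence closes the SF-36 description and carries the only visit schedule for quality of life, so the natural reading is that it tells sites how this outcome is collected.

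The SF-36 is the trial's only quality-of-life instrument. Someone building the case report form from the recording sentence would print a VAS line. Someone building it from the list of secondary outcomes would print the questionnaire. With two hospitals recruiting (section 2.1), the two could even differ. A questionnaire not given at a visit cannot be reconstructed from a VAS mark at the analysis stage, so a statistical analysis plan could not repair the gap.

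**Working it through.** The protocol states no figure on this point that could be reproduced. The check compares sentences and adds a count.

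**Inputs**
- Scales listed for the SF-36: 8 (section 2.5.2).
- Quality-of-life assessments per patient: 4, at weeks 1, 6, 10 and 14 (section 2.5.2).
- Values from one VAS rating: 1.
- Planned patients: 300, as 100 in each of three arms (section 2.2.2).

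**Step 1: what each statement would deliver per patient**

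| Statement followed | Scores per visit | Visits | Scores per patient |
|---|---|---|---|
| SF-36 scored into its listed scales | 8 | 4 | 8 × 4 = 32 |
| Quality of life on a single VAS | 1 | 4 | 1 × 4 = 4 |

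One number per visit cannot be resolved into eight. The two statements therefore describe different data sets.

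**Step 2: does other text resolve the conflict?**
- The list of secondary outcomes has no quality-of-life VAS, so the sentence does not describe a separately declared endpoint.
- The defined VAS measures pain and is tied to the primary outcome.
- If the VAS sentence is set aside as an error, the article gives the SF-36 no visit schedule of its own, because the sentence with the RMDQ and ODI visits does not mention it.
- Section 2.6 does not mention the SF-36 or quality of life.

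Nothing in the article decides between the two statements.

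**Step 3: the most that could be affected**
- Planned quality-of-life assessments: 300 × 4 = 1,200, or 100 × 4 = 400 per arm.
- This ceiling assumes full recruitment, no dropout, and a VAS used in place of the questionnaire for every patient at both hospitals. If both hospitals hand out the SF-36, the number affected is 0. The documents do not show where between 0 and 1,200 the trial lies.

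**Step 4: what is not touched**
- The primary outcome is pain on a 100-mm VAS, for which the recording method fits.
- The RMDQ and ODI are named as the instruments used at their visits.
- The planned 300 patients and the significance level in section 2.6 ("the statistical significance level will be considered to be 0.05 (2-sided), with 95% confidence intervals") play no part in the contradiction.

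**The case against.** The strongest reply is that this is a drafting slip. The quality-of-life sentence nearly repeats the pain sentence, so wording may have been carried over from the primary outcome. The section still commits to the SF-36 by name, describes it as the quality-of-life instrument and lists its scales. One misplaced phrase need not override all of that. This is an inference, but a reasonable one, and it bears on how likely harm is. It does not remove the contradiction: the printed method is still wrong for the instrument, and a slip is all the easier to correct.

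A reader might go further and infer that, followed as written, the trial collects no SF-36 data and loses this outcome beyond recovery. The documents do not support that. The VAS sentence speaks of quality of life and does not say that the SF-36 form is replaced. Following the plan as written means facing two conflicting instructions. The case report form is not shown, so which one the sites follow is unknown.

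Two further replies deserve weight. First, the article condenses a fuller protocol, which may well leave out detail such as VAS anchors. That is accepted, and missing anchors are not raised as a fault. The point is not an omission, because the article states a method and that method does not fit. Second, only one of four listed secondary outcomes is involved. That stands, and it sets the severity.

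**Conclusion.** The point holds as an internal contradiction in section 2.5.2. An eight-scale questionnaire is the named outcome, a 100-mm VAS is the stated recording method, and the second cannot produce the first. That much needs no assumption beyond the text.

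The consequence is conditional. SF-36 scale scores would be missing wherever a VAS was collected in place of the questionnaire, up to a ceiling of 1,200 planned assessments. That ceiling should not be read as an expected loss. Severity is lower: one secondary outcome is at risk, while the primary outcome and the sample size are unaffected. Confidence is high for the contradiction. Whether any data are actually lost cannot be judged from this document.

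**What to change.** Replace the quality-of-life sentence in section 2.5.2 with a statement that participants complete the 36-item SF-36 at weeks 1, 6, 10 and 14, and that it is scored into its eight scales. This also gives the SF-36 an explicit visit schedule, as the RMDQ and ODI already have.

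Check the case report form at both hospitals against the corrected sentence. If a VAS has been used in place of the questionnaire for some visits, report how many, and do not present those ratings under the SF-36 name.

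If a quality-of-life VAS is also wanted, list it as a separate secondary outcome and define it there.

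The cost is one sentence of protocol wording and a form check at two sites. Sample size, randomization and the primary analysis do not change.

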### 2.6.
*Statistical analysis*

After the experiment is completed, we will establish an experiment-related database. The software of SPSS, version 21 (SPSS Inc. Chicago, IL) will be used for statistical analysis, and measurement data will be expressed by Mean and Standard Deviation (mean ± SD). The independent t-test and Chi-square test will be used to compare differences in general characteristics between the groups. All statistical analyses will be performed using PASW statistics 18 for Windows, and the statistical significance level will be considered to be 0.05 (2-sided), with 95% confidence intervals.

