Continuous and controllable lumbar traction can: reduce the pressure in the intervertebral disc; alleviate the pressure of the lumbar facet joints to correct the disorder of the facet joints, and balance the various muscle groups of the lumbar spine to achieve its effective biomechanics effects. Self-gravitation traction is 1 of them.^[21]^ Thus, our team has developed a self-gravitation traction device to achieve continuous and controllable lumbar traction. The aim of this RCT is to evaluate the effectiveness and safety of the self-gravitation traction device on treating LDH and to confirm the positive effect of the device on the treatment of LDH.

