#### 2.2.2.
*Sample size*.

Prior to launch the study officially, a pilot feasibility study (unpublished material) is conducted. Sample size calculation is based on the effective size of the pilot feasibility study. Finally, the study plan is to recruit 300 patients and distribute them at a ratio of 1:1:1, with 100 cases in each group.

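### The article does not settle whether the 40% and 60% arms are separate or pooled, and names no primary contrast; unadjusted tests at its flat 0.05 would carry a 9.1% or 12.2% error rate

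*Protocol article*

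**What the plan says.** Five places in the protocol article bear on which arms are compared.

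- Section 2.1 (Trial design): "This trial is designed as a pragmatic double-center, single-blind, and 3-arm (1:1:1 ratio) RCT". The same section then has patients "randomly allocated into the intervention group (traction load is 40% or 60% of their body weight) or control group". The first statement gives three arms, the second a two-way split. The Abstract uses the same two descriptions.
- Section 2.3 (Randomization and blinding): before analysis, the first unblinding releases a group code, with experimental or control as the example. The three specific interventions are learned only after analysis.
- Section 2.5.2 (Clinical outcomes): "Change from baseline after 6 sessions of treatment will be compared between the groups as the primary outcome". No contrast is named. The same section marks week 6 as the primary endpoint, and that time point is used here; the count of sessions in the sentence is a separate matter.
- Section 2.6 (Statistical analysis): "The independent t-test and Chi-square test will be used to compare differences in general characteristics between the groups", and, for all analyses, "the statistical significance level will be considered to be 0.05 (2-sided), with 95% confidence intervals". No test is named for the primary outcome.
- Section 1 (Introduction): the aim includes "to confirm the positive effect of the device on the treatment of LDH", a single claim about the device. Section 3 (Discussion), by contrast, stresses finding the best traction dose, which needs the loads kept apart.

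Section 2.2.2 gives the size: "the study plan is to recruit 300 patients and distribute them at a ratio of 1:1:1, with 100 cases in each group".

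**The concern.** Which arms are compared defines the trial's question, and the article answers it in two ways. Pooling 40% and 60% against 20% asks whether higher load in general helps. Separate contrasts ask whether each load helps.

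The error rate and the power depend on the choice. With separate contrasts each at 0.05, the single claim about the device gets two chances of success, or three if 40% v 60% also counts. With pooling there is one chance, but a load that works can be masked by one that does not. The independent t-test gives no guidance: in a three-arm trial it must be run either on pairs or on merged arms. If the choice were made after results by arm had been seen, the 0.05 level would no longer describe the claim.

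**Working it through.** **Inputs from the article.** Three arms, 1:1:1, 100 per arm (2.1, 2.2.2); two-sided 0.05 for all analyses (2.6). The basis of the 300 patients cannot be reproduced: "Sample size calculation is based on the effective size of the pilot feasibility study", and no effect, SD, power or dropout is given.

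**Assumptions, not in the article.** The number of primary contrasts (one, two or three); that any significant contrast counts as success; and, for the last step only, an SD of 25 mm for VAS change.

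**1. The stated level.** One test at critical value 1.960 has an error rate of 5.0%. This applies to a single omnibus test of three arms or a single pooled contrast.

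**2. Two contrasts against the shared 20% arm, each at 0.05, all arms truly equal.** With equal allocation the two test statistics have correlation 0.5. With c = 1.960,

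FWER = 1 − ∫ φ(u) [Φ(u + c√2) − Φ(u − c√2)]² du = 0.0907, or **9.1%**.

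Simulated t-tests with 100 per arm (200,000 runs) give 9.0%.

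**3. All three pairs, each at 0.05.** This is the upper tail of the studentized range for three groups at q = 1.960 × √2 = 2.772, which is 0.122, or **12.2%**. Simulation gives 12.2%.

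**4. After control.** Dunnett for two contrasts: critical z 2.212, nominal level about 0.027 each, overall 5.0%. Bonferroni for two (0.025 each): 4.6%. Bonferroni for three pairs (0.0167 each): 4.4%.

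**5. What pooling does to power.** Suppose one load works and its own contrast has 80% power, so its expected z is 1.960 + 0.8416 = 2.80. Suppose the other load has no effect.

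- Pooling halves the mean difference.
- The variance factor changes from 1/100 + 1/100 = 0.02 to 1/200 + 1/100 = 0.015.
- Expected z = 2.80 × 0.5 × √(0.02/0.015) = 1.62.
- Power = Φ(1.62 − 1.96) ≈ **37%**.

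If instead both loads work equally well, expected z = 2.80 × √(0.02/0.015) = 3.23 and power is Φ(3.23 − 1.96) ≈ 90%. Pooling gains only when the loads act alike.

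**6. Price of control.** Difference detectable with 80% power = (z + 0.8416) × 25 × √(2/100).

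- At 0.05: 2.8016 × 3.536 = 9.9 mm.
- With Dunnett: 3.0537 × 3.536 = 10.8 mm.
- Ratio: 3.0537 / 2.8016 = 1.09, about 9% more. The ratio does not depend on the assumed SD.

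**The case against.** The strongest reply is that the article plans no inflated test. The t-test and chi-square sentence is confined to baseline characteristics, no efficacy test is named, and a full protocol or SAP not shown here may hold the model and the multiplicity method. A two-sided 0.05 is conventional, and the article claims no family-wise rate. Read as two groups, section 2.1 gives one contrast and no inflation.

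Much of this stands. A reader might infer that the trial's false-positive rate is 9 to 12%, or that efficacy will be tested by pairwise t-tests. The article supports neither: the rates it allows run from 5.0% to 12.2%, depending on a choice it does not make. Four further limits apply:

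- The chi-square test is not a two-group test; it handles a table with three columns.
- Counting many secondary false positives would require testing every scale, visit and pair, which the article does not plan.
- Baseline p-values are uninformative in a randomised trial, but they change no primary result.
- The 37% is an illustration with one inert load, not a measure of a planned analysis.

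The reply does not remove the point. A missing multiplicity method alone would be no finding. Here the article does describe the comparison, in sections 2.1, 2.3 and 2.5.2, in ways that fit both two groups and three. Any SAP would have to choose between these statements, and the choice changes what the trial can conclude.

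**Conclusion.** The point holds in conditional form. The article does not settle whether the higher loads are pooled or separate and fixes no primary contrast, while setting one flat 0.05 for everything. If two contrasts against 20% are each tested unadjusted and any success supports the claim, the family-wise error is 9.1%; with all three pairs it is 12.2%. One omnibus or pooled test holds 5%, but the pooled test can fall to about 37% power for a load that would have 80% on its own. The error rates assume equal arms in truth, equal allocation and approximately normal test statistics; the power figure assumes that the other load has no effect. Classed as a cheap improvement: the change is one of wording, and it decides which claim the trial can make.

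**What to change.** Before any outcome is seen by arm, bring four sections into line.

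- **2.1:** state that the three arms are analysed separately, and drop the wording that merges 40% and 60% into one group.
- **2.3:** state that the first unblinding releases three codes. The contrasts need the 20% arm to be identifiable, and a fixed sequence also needs the other two told apart.
- **2.5.2:** name 60% v 20% and 40% v 20% on week-6 VAS change as the two primary contrasts.
- **2.6:** specify one linear model for week-6 VAS change with arm as a three-level factor. Control the two contrasts at 0.05 overall, by Dunnett (about 0.027 each) or a pre-stated fixed sequence. Report 40% v 60% and the secondary outcomes as estimates with 95% confidence intervals.

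No extra patients or data are needed. With Dunnett, the detectable difference at 80% power rises about 9%, for example from 9.9 to 10.8 mm at an assumed SD of 25 mm with 100 per arm. A fixed sequence keeps 0.05 for the first contrast, but the second can be claimed only if the first succeeds. If the sponsor wants 40% v 60% as a confirmatory question, as the Discussion's interest in dose might suggest, all three pairs need control. Bonferroni at 0.0167 each raises the detectable difference from 0.396 to 0.458 SD.
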